**Table 1 – Intervention, administration, dose and supplier**

| **Intervention** | **Administrative route** | **Dose** | **Supplier** |
| --- | --- | --- | --- |
| Metformin MR | Oral | - 500mg once a day for 7 days. - Telephone call for assessment of side effects. If no concerns proceed to - 1500mg once a day for 21 days | Clinical Research Facility Pharmacy |
| Spermidine | Oral | - 15mg for 21 days | Longevity Box |
| Fisetin | Oral | - 100mg for 21 days | Longevity Box |

[figure not shown]

1. Study setting

This is single site study at the University Hospitals Birmingham NHS Foundation Trust. Healthy volunteers will be recruited using established networks. The Clinical Visits will be in the Clinical Research Facility (CRF) at the University of Birmingham. This is based at Queen Elizabeth Hospital Birmingham.

1. Participant Recruitment

Eligibility Criteria

The study population is healthy older people.

Inclusion criteria

- Age ≥70 years.
- Ability to provide informed consent.
- Able to travel to the clinic for initial and subsequent evaluations.
- Ability to understand spoken and written English

Exclusion criteria

- Current smokers, or ex smokers who have stopped within the last 12 months, or are using nicotine replacement products.
- History of diabetes (type 1 or 2), or untreated vitamin B12 deficiency.
- Untreated thyroid disorder.
- Active cancer - currently on treatment or palliative .
- Major illness, surgery or trauma in last 60 days.
- Recent infection in last 60 days.
- Allergies or intolerance to any of the drugs to be studied.
- Any contraindication to metformin MR, as listed in the current summary of medicinal product characteristics for metformin MR.
- Any medication which significantly interacts with metformin MR, as listed in the current summary of medicinal product characteristics for metformin MR.
- Currently taking any of the following medications, which confound the effects of inflammation: Tamoxifen, Cyclosporine A, immunosuppressants or Anti TNF inhibitors, Non-Steroidal Anti-Inflammatory Drugs (NSAIDs).
- Currently taking any of the following anticoagulant drugs (blood thinners): Warfarin, Direct oral anticoagulant drugs (DOACs), low molecular-weight heparin, clopidogrel, or high-dose aspirin. Patients taking low dose ≤75mg aspirin only may be recruited.
- Individuals at risk of bleeding complications, including those with inherited bleeding disorders (such as haemophilia), or previously unexplained haemorrhage.
- Unable or unwilling to maintain current lifestyle throughout study such as eating habits, exercise habits, etc.
- Estimated glomerular filtration rate <45 mL/min/1.73 m2 by the Modified Diet in Renal Disease 4 (MDRD4) or Chronic Kidney Disease - Epidemiology collaboration (CKD-EPI) equation.
- History of diarrhoeal illness within the last three months (>48 hours of Bristol stool chart grade 6 or 7).
- Liver function tests (bilirubin, alanine aminotransferase or alkaline phosphatase) >3× upper limit of normal.
- Symptomatic chronic heart failure, diagnosed according to European Society of Cardiology guidelines (asymptomatic left ventricular systolic dysfunction will not be an exclusion criterion).
- Life expectancy of <3 months as adjudicated by the local Investigator.
- Previous inclusion in study investigating effects of ‘geroprotector’ medication in last six months.
- Allergy to local anaesthetic.
- Coeliac disease (spermidine only) {Loh, 2013 #148}

Recruitment target

The target recruitment is 60 healthy volunteers to start the medication. It is anticipated that following inclusion bloods a few volunteers may have to be excluded as they will no longer fulfil the inclusion and exclusion criteria.

Recruitment technique

Participants will be invited by contact through the 1000 Elders database. The 1000 Elders is a database of research active healthy older people who have consented to be contacted about studies run through the University of Birmingham. Names, addresses and contact details (telephone and email) are stored complying fully with the Data Protection Act 2018 legislation. The invitation will be in the form of an email. This will include an attached PIS, summary of the study, and an invitation to contact the research team if they would be interested in taking part in the study. The study will also be advertised through a public facing website and through local networks.

The Be Part of Research Volunteer network will send out study information and study contact details on our behalf to their network of volunteers. Interested volunteers will contact the study team for further information.

Participants will be reimbursed £200 for their involvement within the study. Payment will be made to all those recruited to the study. Anyone who attends for the initial visit but is not eligible for recruitment to the study or changes their mind after discussion with the study team will receive reimbursement for their travel to the visit – maximum of £20.

Recruitment

Potential participants will contact the study team via email or telephone to express an interest to join the study. Potential participants will then be invited to the Clinical Research Facility at Queen Elizabeth Hospital Birmingham for the initial visit.

Consent

At the initial visit eligibility will be confirmed and informed consent will be gained for all activities in the study. The nature and objectives of the study will be explained, and potential risks discussed. This information will be presented in a written patient information sheet (PIS) sent to potential participants prior to the in person visit, giving participants time to consider their participation. The process for withdrawal, including the subsequent impact on data and sample storage will be described.

At this point capacity to consent to be in the study will be assessed using the Mental Capacity Act. Participants will then sign a written consent form, and a copy of the information sheet and consent form given to them, and other copies stored in the study file. At the subsequent visit the participant’s willingness to continue in the study will be ascertained. Throughout the study the participant will have the opportunity to ask questions about the study. Any new information that may be relevant to the participant’s continued participation will be provided.

1. Study procedures

Table 1 demonstrates the timing of the individual assessments/procedures that will be conducted as part of this study.

Table 2 – Timing of individual procedures involved in this study

|  | **Initial assessment** | **Day 0 Visit** | **Day 7 - Phone Call (Metformin MR only)** | **Phone Call**  **(Day 10/17)** | **Post-intervention assessment**  **(Day 28/35)** | **Qualitative Interviews** |
| --- | --- | --- | --- | --- | --- | --- |
| Timing |  | Up to 7 days post initial assessment |  | +/- 3 days of 10/17 | +3 days of 28/35 | Up to 3 months from Day 28/35 |
| Informed consent | X |  |  |  |  | x |
| Co-morbidities and medications | X |  |  |  |  |  |
| Barthel Index | X |  |  |  |  |  |
| Nottingham Extended Activities of Daily Living | X |  |  |  |  |  |
| Frailty assessment | X |  |  |  |  |  |
| Handgrip strength | X |  |  |  |  |  |
| Short Physical Performance Battery | X |  |  |  |  |  |
| Three-day food record | X |  |  |  |  |  |
| Ultrasound quadriceps | X |  |  |  |  |  |
| Bioelectrical Impedance Analysis | X |  |  |  |  |  |
| Montreal Cognitive Assessment (MoCA) | X |  |  |  |  |  |
| Stool collection | X |  |  |  | X |  |
| EEG | X |  |  |  | X |  |
| Venepuncture | X | X |  |  | X |  |
| Adipose biopsies |  | X |  |  | X |  |
| Adverse event reporting | X | X | X | X | X |  |
| Drug distribution |  | X |  |  |  |  |
| Compliancy pill count |  |  |  |  | X |  |
| Qualitative Interview |  |  |  |  |  | X |

Co-morbidities and medications

Co-morbidities and medications will be recorded using check boxes for frequently encountered conditions and medications with the option for free text to record less common co-morbidities and medications.

Handgrip strength

Handgrip strength will be measured using a handheld dynamometer (Jamar, Takei Grip D, or other calibrated device). Where the participant can sit out in a chair, handgrip strength will be measured with the arm flexed at 90^O^ at the elbow and the forearm supinated. If the participant cannot sit out and measurements are taken in the bed, this will be recorded and measurements will instead be performed in the most upright position that is feasible. Participants will be asked to “squeeze as hard as [they] can”. Handgrip strength will be measured twice on each side and the best recording of all will be used for analysis (29).

Short physical performance battery

The Short Physical Performance Battery (SPPB) is a standardised measure of physical performance that has been shown to be sensitive to change and provides an objective measure of physical function (30). SPPB consists of usual gait speed, side-by-side stand, semi-tandem stand, tandem stand, and five chair stands. A total score of 12 is derived, with a lower score representing reduced physical performance. SPPB will be measured within 48 hours of admission and 48 hours of discharge. Gait speed will be measured by asking the participants to walk a four-metre course at their “usual pace”. Participants will be asked to complete five chair stands “as quickly as [they] can” (see Appendix). If it is not possible to measure gait speed or any part of the SPPB at any planned visit the reasons for this will be recorded (e.g., if either the investigator or the participant considers it unsafe to do so). The need or use of a mobility aid will be recorded. It is recommended that the SPPB should be performed after assessment of muscle quantity/quality (ultrasound quadriceps and bioelectrical impedance analysis), to ensure that these assessments are not affected the effect of exercise.

Activities of Daily Living (ADL) assessment

The Barthel Index (Appendix) (31) and Nottingham Extended Activities of Daily Living (see Appendix) (32) will be completed for participants. This information can be gathered from asking the participant themselves. The Nottingham Extended Activities of Daily Living can be provided to the participant to complete themselves as a questionnaire where they are able to do so.

Frailty assessments

Frailty will be defined using three definitions: 1) Clinical Frailty Scale 2) Fried phenotype 3) Frailty Index. The Clinical Frailty Scale (CFS) assesses frailty on a 9-point scale (Appendix). CFS will be assessed by the investigator by reviewing the clinical records and an overall holistic assessment of the participant, considering the results of the ADL assessment above. The Fried phenotype will be assessed utilising information collected from assessment of handgrip strength and gait speed, and directly asking the participant about weight loss, physical activity, and self-reported exhaustion (Appendix). The frailty index will be calculated from information collected in the study elsewhere, with direct questioning where necessary (Appendix).

Cognitive testing

Cognitive testing will be performed using the Montreal Cognitive Assessment (MoCA) (33).

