**Resilience PROmotion using GeRoprotectors: AssessMent of biological effect (REPROGRAM study)**

1. Background

Doubling of life expectancy in the last 200 years is testament to success of public health and medical advances. However, population ageing presents a major health and social care challenge. As we age, our biological systems and clinical features become increasingly diverse. This diversity can lead to either healthy ageing or development of age-related conditions such as frailty, sarcopenia, and cognitive decline (1). Advancement of age is associated with reduced resilience, hindering the ability to maintain balance and stability when confronted with infections, falls, or surgery (2). This loss of dynamic resilience with age, whilst universally recognised, is poorly defined or understood biologically, limiting our ability to intervene to maintain health in old age.

Advances in ageing biology have enabled the description of key biological mechanisms driving the aged phenotype, the hallmarks of ageing (3), including: reduced mitochondrial fitness, telomere shortening, reduced autophagy, accumulation of senescent cells, microbial dysbiosis and increased systemic inflammation. Importantly, targeting these ageing processes, for example by deleting senescent cells (4), extends healthspan in mice, reducing development of age-related conditions. Geroprotectors are drugs which can affect underlying ageing processes rather than a single symptom or disease. However, there is an absence of robust pharmacodynamic and pharmacokinetic data on their ability to modify the proposed targets in vivo in humans. Additionally, it is unclear which patients should be treated and where in their life-course the drugs will have the optimum effect (5).

This study aims to investigate three different agents, metformin, fisetin and spermidine, and determine their ability to modify biological pathways in vivo in humans. These agents have been chosen as drugs with both evidence of effect on the hallmarks of ageing and good safety profiles in frail, older adults. Metformin, an oral hypoglycaemic agent, has been used safely in frail, older adults for over 60 years (6). Fisetin, a plant flavonol, and spermidine, a natural polyamine, can both be bought as a supplement in the UK and have no reported side effects (7) (8, 9).

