Conditions that were previously unknown to the participant may be identified during the process of research data collection; this could be considered both a beneficial and unfavourable consequence. In the case of potentially significant findings, these will be explained to the participant, including the potential consequences and further investigations or treatment that might be indicated. These findings will be relayed to the participants’ General Practitioners (GP) or secondary care medical team, who will be advised to arrange further management or to refer to appropriate specialties; this is usual practice in the United Kingdom (UK). Specific consent for findings to be communicated with their GP or medical team will be gained from the participant; the GP will be informed routinely of recruitment to this study. As the researchers will have a dual role as clinicians working within the NHS trust, it may sometimes be appropriate for the clinicians to arrange further investigations, management, or follow-up, but such decisions should be clearly communicated to the wider NHS team. It should be clarified to the participant that any investigations or management are separate from the research study and are part of NHS care.

The study will fit within existing ethical and regulatory frameworks. Participants are healthy volunteers, and not recruited as NHS patients. However, as the recruitment and assessments will take place within an NHS institution we will secure approval through the Health Research Authority (HRA) and an NHS Research Ethics Committee (REC).

Drug Intervention

Metformin has a long history of use in older adults and the safety profile is good (6). Metformin will be used off-licence. It is licensed only for use in type 2 diabetes but is also commonly used for polycystic ovary syndrome and type 1 diabetes. The drug will be started slowly and the target dose reached over a week to minimise side effects. There will be a telephone call after a week to assess any side effects and to decide whether to continue with the intervention or to withdraw the participant from the study. Spermidine and fisetin are supplements which are available “over the counter” in the UK. The doses have been chosen to mimic doses in recent studies (ref – Senokowitsch, 2023) and also available supplements. There are no known side effects reported in the literature (Wu, 2020, spermidine – a comprehensive review of spermidine)(9).

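### The exclusion criteria admit people who already buy and take fisetin or spermidine, so in those two arms the baseline biopsy may already be treated and the before/after change diluted

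*Protocol*

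**What the plan says.** - **Availability.** Background states that fisetin and spermidine "can both be bought as a supplement in the UK and have no reported side effects". Drug Intervention, under Assessment and management of risk, repeats the point: "Spermidine and fisetin are supplements which are available “over the counter” in the UK". It adds, "The doses have been chosen to mimic doses in recent studies", and the same sentence names marketed supplements as a second source for the doses.
- **Prior exposure.** In the exclusion criteria, the only item on earlier geroprotector exposure is "Previous inclusion in study investigating effects of ‘geroprotector’ medication in last six months". The list of excluded confounding medications is closed (tamoxifen, ciclosporin, immunosuppressants, anti-TNF agents, NSAIDs) and contains neither agent.
- **Lifestyle.** A further exclusion reads "Unable or unwilling to maintain current lifestyle throughout study such as eating habits, exercise habits, etc".
- **Recording.** Under Co-morbidities and medications: "Co-morbidities and medications will be recorded using check boxes for frequently encountered conditions and medications with the option for free text". Table 2 marks this item at the initial assessment only. The pill check at Day 28/35 concerns the supplied study drug.
- **Design and outcome.** The study is open label with no untreated arm. The primary outcome is the SA-β-Gal senescent cell count in adipose tissue after three weeks, adjusted for the count before treatment.
- **Size.** Power Calculations gives 9 participants for 80% power at a significance level of 0.05 and a mean difference of 5%. It recruits 10 of each sex, 20 in all, per agent.

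**The concern.** Someone who received spermidine in a study five months ago is excluded. Someone who bought it and took it this morning is not. The criterion therefore misses the exposure that the protocol itself describes as freely available, at doses chosen partly to match what is on sale.

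This matters because the design has no untreated control. Evidence for each agent rests on the change from a baseline that is assumed to be untreated. If a spermidine user is allocated spermidine, or a fisetin user fisetin, the Day 0 biopsy already reflects the agent and little further change can be expected. That pulls the arm's mean change towards zero and adds spread. With supplements not named on the medication record and no second record at Day 28/35, such a participant could go unnoticed, as could one who starts a supplement during the study.

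**Working it through.** **1. Does any provision close the gap?** The medication list names neither agent. The metformin contraindication and interaction criteria point to the metformin product information and do not name them. The allergy criterion concerns intolerance, not use. There is no washout and no instruction to avoid the agents. The gap stands.

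**2. Which arms are exposed to dilution?** It is clearest when the participant's own agent is the allocated agent. For metformin this is implausible: it is prescribed, and diabetes, its licensed indication according to Drug Intervention, is an exclusion. That leaves the spermidine and fisetin arms.

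**3. The plan's own figure.** The protocol states no standard deviation, sidedness or test, so n = 9 cannot be reproduced forward. Back-solving a two-sided paired t-test (noncentral t, α = 0.05, 80% power, n = 9) gives a standardised effect d = 1.067. A 5-point difference then implies an SD of change of 5 / 1.067 = 4.69.

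**4. Dilution.** Let a fraction f of the arm already take its allocated agent and show no further change.
- Mean change = 5(1 − f)
- Variance of change = 4.69² + f(1 − f) × 5²
- f = 0.10: mean 4.5, SD = √(21.96 + 2.25) = 4.92
- f = 0.20: mean 4.0, SD = √(21.96 + 4.00) = 5.10

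The lower figure in each range below uses this variance. The upper figure shifts the mean only and keeps the SD at 4.69.

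| n analysed | none exposed | 10% exposed | 20% exposed |
|---|---|---|---|
| 9 (sizing figure, one sex) | 80% | 67–71% | 54–61% |
| 10 (recruited per sex) | 85% | 73–77% | 60–67% |
| 20 (recruited per agent) | over 99% | 97–98% | 91–95% |

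A simulation with 100,000 replicates per cell agreed with the lower figures to within about half a percentage point. To restore 80% power with the mixture variance, a single-sex group would need 12 participants at 10% exposed and 15 at 20%.

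**5. Status of f.** The protocol gives no prevalence of use. The 10% and 20% are illustrations: one and two people in a cell of ten.

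**The case against.** Four stronger readings are tempting, and the protocol does not support them.

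- **That participants are told to keep taking their supplements.** The lifestyle criterion names eating and exercise habits and does not mention supplements. That a user would continue is a reasonable inference, not an instruction.
- **That a user of one agent allocated to another shows change caused by the wrong agent.** Stable use is present at both biopsies and does not by itself create a before/after change. The baseline may be altered and an interaction is possible, but the effect on the change is uncertain.
- **That all three arms are diluted.** Realistically only the spermidine and fisetin arms are.
- **That power generally falls to between 54% and 71%.** Those values hold only at n = 9. The primary question is asked per agent, and with both sexes pooled the loss is small. The single-sex figures remain relevant because Power Calculations sizes the study by sex.

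Two further points have weight. Zero further change in exposed participants is a worst case, and true use may be too rare to matter. The free-text medication field could also pick up some users before Day 0. That protection is partial, since supplements are not asked about and the record is not repeated. An analysis plan could specify how known users are handled, but it cannot adjust for exposure that was never recorded, and eligibility is a protocol matter.

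**Conclusion.** The point holds as a gap in the eligibility criteria and in the recording of concomitant use. A current purchaser of fisetin or spermidine can be enrolled and randomised to the same agent, with a treated baseline in an uncontrolled before/after comparison.

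Its size cannot be settled from the protocol. Under the stated assumptions, 10% to 20% exposed would cost a single-sex group of ten roughly 8 to 25 percentage points of power (85% down to between 77% and 60%). It would cost a pooled arm of twenty at most about 8 points (over 99% down to 91%). Lower use, or some further response in exposed participants, would cost less. This is a worthwhile and inexpensive improvement; it does not show that the trial's result will be invalid.

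**What to change.** 1. Extend the existing exclusion so that it covers inclusion in a geroprotector study and also current or recent own use of metformin, fisetin or spermidine, including over-the-counter supplements. The six-month window already in the protocol is one option, but it was written for study participation. The sponsor should set and justify the period.
2. Ask participants not to start any of these agents on their own during the study.
3. Name supplements on the medication record, and complete that record at both the initial and Day 28/35 visits.
4. Plan a sensitivity analysis of the primary outcome without exposed participants. Section 8.1 shows that recruitment is under way, so include those already enrolled where their use can be ascertained.

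The cost is a revised eligibility line, a participant instruction, a CRF question asked twice, and a few volunteers lost at screening.
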